## Abstract

**Background:**

Patients after kidney transplantation eventually face the risk of graft loss with the concomitant need for dialysis or retransplantation. Choosing the right kidney replacement therapy after graft loss is an important preference-sensitive decision for kidney transplant recipients. However, the rate of conversations about treatment options after kidney graft loss has been shown to be as low as 13% in previous studies. It is unknown whether the implementation of artificial intelligence (AI)–based risk prediction models can increase the number of conversations about treatment options after graft loss and how this might influence the associated shared decision-making (SDM).

**Objective:**

This study aims to explore the impact of AI-based risk prediction for the risk of graft loss on the frequency of conversations about the treatment options after graft loss, as well as the associated SDM process.

**Methods:**

This is a 2-year, prospective, randomized, 2-armed, parallel-group, single-center trial in a German kidney transplant center. All patients will receive the same routine post–kidney transplant care that usually includes follow-up visits every 3 months at the kidney transplant center. For patients in the intervention arm, physicians will be assisted by a validated and previously published AI-based risk prediction system that estimates the risk for graft loss in the next year, starting from 3 months after randomization until 24 months after randomization. The study population will consist of 122 kidney transplant recipients >12 months after transplantation, who are at least 18 years of age, are able to communicate in German, and have an estimated glomerular filtration rate <30 mL/min/1.73 m^2^. Patients with multi-organ transplantation, or who are not able to communicate in German, as well as underage patients, cannot participate. For the primary end point, the proportion of patients who have had a conversation about their treatment options after graft loss is compared at 12 months after randomization. Additionally, 2 different assessment tools for SDM, the CollaboRATE mean score and the Control Preference Scale, are compared between the 2 groups at 12 months and 24 months after randomization. Furthermore, recordings of patient-physician conversations, as well as semistructured interviews with patients, support persons, and physicians, are performed to support the quantitative results.

**Results:**

The enrollment for the study is ongoing. The first results are expected to be submitted for publication in 2025.

**Conclusions:**

This is the first study to examine the influence of AI-based risk prediction on physician-patient interaction in the context of kidney transplantation. We use a mixed methods approach by combining a randomized design with a simple quantitative end point (frequency of conversations), different quantitative measurements for SDM, and several qualitative research methods (eg, records of physician-patient conversations and semistructured interviews) to examine the implementation of AI-based risk prediction in the clinic.

**Trial Registration:**

ClinicalTrials.gov NCT06056518; https://clinicaltrials.gov/study/NCT06056518

**International Registered Report Identifier (IRRID):**

PRR1-10.2196/54857

## Introduction

Shared decision-making (SDM) is increasingly important in health policy and clinical practice. Over the past decades, researchers, patient advocates, and policymakers all over the world have increased efforts to shift health care from a paternalistic to a patient-centered approach, focusing on the patient as a person [1,2]. Kidney transplantation is the most frequently performed solid organ transplantation and although the application of SDM prior to kidney transplantation has been discussed, little is known about how to improve SDM after transplantation [3]. This is surprising as there are numerous potentially preference-sensitive decisions that patients, support persons, and physicians have to make in this setting, for instance relating to the management of comorbidities, effects of treatment on fertility, use of immunosuppressant drugs, and resulting second cancers [4,5].

In patients with chronic kidney disease, choosing the right kidney replacement therapy and the optimal timing for kidney replacement therapy is an important preference-sensitive decision. Implementing SDM has been shown to leave more patients satisfied with their choice of dialysis modality [6]. Not only the modality itself but also details like the vascular access and the specific dialysis regimen are preference-sensitive and should be part of an SDM process that also considers age-dependent needs [7-9].

Since most patients after kidney transplantation eventually face the risk of graft loss with the concomitant need for dialysis or retransplantation, comparable considerations should be applied to kidney transplant recipients at risk for graft loss. However, the rate of conversations about treatment options after kidney graft loss is as low as 13% in conventional physician-centered care settings [10]. This leaves room for optimization with respect to the frequency of conversations as well as the associated SDM process. While care-based interventions have shown to be effective in increasing the frequency of conversations about treatment options after graft loss, it is unknown whether the implementation of artificial intelligence (AI)–based risk prediction models can have such influence on physician-patient interactions [10].

Different risk prediction models for graft loss using methods of statistics or AI have been introduced and show good predictive performance [11,12]. More importantly, they are more accurate than experienced physicians in predicting risks for graft loss [11,13]. Implementing such models into routine care could indicate patients at risk for graft loss and thereby increase the frequency of conversations about treatment options after graft loss. However, little is known about the impact of AI-based interventions on the interaction between patients, support persons, and physicians [14].

While there are several studies discussing the potential of AI to support SDM in the bioethical literature [15], there is a lack of empirical studies to systematically investigate the impact of AI on SDM [16].

In this study, we aim to evaluate the influence of an AI-based risk prediction model for 1-year risk of graft loss on the frequency of conversations about treatment options after graft loss, as well as the associated SDM process, in patients who had kidney transplants with low estimated glomerular filtration rate (eGFR).

## Methods

### Study Design and Setting

The Prospectively investigating the Impact of AI on Shared Decision-Making in Post-Kidney Transplant Care (PRIMA-AI) trial is a 2-year, prospective, randomized, 2-armed, parallel-group, single-center trial in a German kidney transplant center (KTC). Patients more than 12 months after kidney transplantation with eGFR <30 mL/min/1.73 m^2^ and support persons will be randomized to routine care or to AI-supported care in a 1:1 ratio. During the study, 5 study visits are planned at the KTC—at randomization, and 3, 6, 12, and 24 months after randomization (Figure 1). In both groups, routine care visits will be scheduled as needed, depending on the patient’s medical condition and time posttransplant, which is usually every 3 months.

**Figure 1 figure1:**
[figure not shown]
Study flowchart summarizing inclusion criteria, interventions, and end points. An estimated number of 122 KTRs will be recruited in the outpatient clinic of a tertiary care center and randomized 1:1 into routine care or AI-supported care and followed up over 24 months. AI: artificial intelligence; eGFR: estimated glomerular filtration rate; KTR: kidney transplant recipient; KTx: kidney transplantation; PROMIS-29: Patient Reported Outcomes Measurement Information System 29; SDM: shared decision-making; Tx: transplantation.

### Recruitment Process

Patients after kidney transplantation regularly undergo routine follow-up at the KTC in an outpatient clinic. Patient data are available in a proprietary electronic health record that allows data extraction for research purposes [17]. Patients who are potentially eligible for the study based on their previous medical data will be contacted via telephone 1 week before their next scheduled appointment and will be asked if they are interested in study participation. If patients are potentially interested, they are provided detailed information about the study by trained study physicians and provide written informed consent after checking inclusion and exclusion criteria at the time of their next outpatient visit at the KTC. Recruitment will occur in the regular outpatient treatment at the KTC by designated study physicians who are not the treating physicians. After recruitment and randomization, the first study visit is performed. No study investigations are performed before written informed consent is obtained from the patients. The KTC is a tertiary care center specializing in kidney transplantation, where approximately 200 kidney transplantations per year are performed.

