### Blinding

Blinding of participants and study staff is not possible given the nature of the intervention.

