#### Intervention Group: AI-Supported Care

The kidney transplant recipients, who are randomized to the interventional arm, will receive identical routine posttransplant care as patients in the control group (see Table 1). In addition, the physicians in the KTC will be provided an AI-based decision support system making predictions for the risk of graft loss based on the patient’s most recent clinical, laboratory, and histopathology data, beginning from the second visit. A previous version of the AI-based decision support system has been studied in silico and in a reader study [11]. The physicians are provided a recommendation on how to proceed in case of a high-risk score. Briefly, physicians are recommended to inform the patients about this risk and discuss the potential necessity of return to dialysis or retransplantation, as well as planning, which mode of renal replacement therapy is preferred by the patient (hemodialysis, peritoneal dialysis, or listing for retransplantation by living donation). Depending on the patient’s preference, preparation for a smooth transition to dialysis or retransplantation should be performed.

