#### Details on Qualitative Research Methodology

##### Overview

The physician-patient conversation will be recorded if physicians, patients, and support persons do not withdraw consent at randomization, as well as 3, 6, 12, and 24 months after randomization. Additionally, patients will be interviewed at randomization, as well as 3, 6, 12, and 24 months after randomization. Data collection at randomization, as well as 12 and 24 months after randomization will be conducted face-to-face, if possible and preferred by study participants. Data collection at 3 and 6 months after randomization will be conducted via telephone. This is to reduce the research-related burden on the participants. It has been suggested that telephone interviews produce similar quality data as face-to-face interviews [33-35]. Also, patients may appreciate being interviewed via telephone as they may feel more relaxed when being interviewed on the telephone and may find it easier to rearrange a telephone interview, rather than having to rearrange a face-to-face interview [36-39]. Participants will be encouraged to tell their views on how the AI-based DSS impacted physician-patient-support person communication and how treatment decisions were made, in the way they prefer, with as little interruption as possible from the interviewer. This narrative approach will help elicit the variety and interplay of potential factors related to treatment discussions [40]. The initial narrative will be followed by semistructured questions which will be developed based on a literature review and discussions among the research team which involves experts in the areas of medicine, communication and behavioral science, health services research, ethics, and medical informatics.

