### Safety

Safety assessments will consist of monitoring and recording all adverse events (AEs) and serious AEs, the regular monitoring of blood chemistry and urine, and regular monitoring of vital signs, physical condition, and body weight. Appropriate sponsor personnel and investigators will monitor the safety of the participants throughout the conduct of the study. AEs mean “any untoward occurrence in a trial subject administered an investigational medicinal product and which does not necessarily have a causal relationship with this treatment” [50]. In the PRIMA-AI trial, subjects will not receive any investigational medicinal product, but physicians will be assisted by an AI-based decision support system. Thus, in this study, an AE can be any unfavorable and unintended sign, symptom, or disease (including concomitant illness), deterioration of a preexisting illness, accident, any suspected drug reaction, or a clinically relevant change of laboratory values whether or not considered to be related to the AI-based intervention. Adverse reactions (ARs) mean “all untoward and unintended responses to an investigational medicinal product unrelated to the dose administered” [50]. In PRIMA-AI, subjects will not receive any investigational medicinal product. Therefore, the definition of AR implies in this trial a reasonable possibility of a causal relationship between the event and the investigational AI-based intervention.

The period of observation for AEs extends from the baseline visit (month 0, visit 1) after informed consent was given until and including month 24 (visit 5). AEs have to be followed up until resolution or stabilization or until the subject’s end-of-study visit (month 24, visit 5), whichever comes first. Preexisting conditions that do not worsen during the course of the study are not reportable as AE. To determine whether a condition has worsened, it is compared to the condition of the subject at baseline visit (month 0, visit 1). All AEs, whether volunteered by the patient, discovered by investigator questioning, or detected through physical examination, laboratory test, or other means will be assessed and recorded in detail in the subject’s file and on the case report form, the AE report form. All AEs will be coded appropriately at the end of the clinical study using MeDRA or, in addition, on request by the study coordinator.

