### Strengths and Limitations

The main strength of this study is the mixed methods approach that will support the analysis of the primary end point with validated assessment tools for SDM and qualitative data from semistructured interviews. It is the first study in the context of kidney transplantation that investigates the impact of AI-based risk prediction on physician-patient interaction. While performed in a tertiary care setting, transplant nephrologists often serve as primary caregivers to kidney transplant recipients. Therefore, the results may generalize to a broader range of care settings as well. The randomized design enables to detect potential effects of the AI-based risk prediction on the conversation frequency about graft loss, which can improve patient information and patient care. It also provides us with a control group, in which SDM about treatment options after graft loss in kidney transplantation can be studied without any intervention, which has not been done so far. Another strength is the long observation time of 24 months, which enables to detect potential adaptations of physicians, patients, and support persons to the novel AI system and the emergence of a sociotechnical system in the recordings of patient-physician interactions as well as the semistructured interviews.

The main limitation is that potential effects of the AI intervention on SDM are indirect since no specific SDM intervention has been implemented and the AI system is not designed to improve SDM in particular, for example, by providing different scenarios or enabling input of patient preferences. Another potential limitation is that participation in the trial may influence physicians to talk about treatment options after graft loss, which may reduce the potential effect size of the AI intervention. Furthermore, the open-label design, which is unavoidable, introduces the possibility of bias, especially since the primary end point is not a medical end point.

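### Randomization is placed before the first study visit in an unblinded trial, so the visit-1 patient-reported measures, which enter the CollaboRATE and CPS end points, are likely to be collected with the arm known

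*Protocol article*

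**What the plan says.** All references are to the protocol article.

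- **Order.** Recruitment Process: "After recruitment and randomization, the first study visit is performed". The same section restricts early assessments only by consent: "No study investigations are performed before written informed consent is obtained from the patients".
- **Visit schedule.** Study Design and Setting: "5 study visits are planned at the KTC—at randomization, and 3, 6, 12, and 24 months after randomization". Table 2 lists consent, eligibility and randomization under Day 0 (visit 1), in the same column as the first CollaboRATE, CPS, PROMIS-29, recall and interview.
- **Qualitative data.** Details on Qualitative Research Methodology, Overview: "patients will be interviewed at randomization, as well as 3, 6, 12, and 24 months after randomization". Recordings of the physician-patient conversation follow the same schedule.
- **Status of visit 1.** Safety treats it as baseline: "The period of observation for AEs extends from the baseline visit (month 0, visit 1) after informed consent was given".
- **Blinding.** Blinding: "Blinding of participants and study staff is not possible given the nature of the intervention".
- **Start of the intervention.** Intervention Group: AI-Supported Care has the AI predictions "beginning from the second visit", which is month 3 in Table 2.
- **Use of visit 1.** Textbox 1 defines the CollaboRATE and CPS end points as means over all study visits from inclusion to month 12 or month 24. Secondary End Points names these two tools as the main secondary measures.

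**The concern.** CollaboRATE and the CPS record how patients see their own involvement in a consultation. Such answers can be influenced by knowing which arm one is in, and so can the consultation itself. If the arm is known at visit 1, the groups may already differ there for a reason unrelated to any AI output.

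Two things are at stake. First, visit 1 is part of the averaged CollaboRATE and CPS end points, so a difference of this kind passes straight into the treatment comparison. Second, the questionnaires, the interview and the recorded conversation lose their value as a comparator from before allocation, for the baseline description and for the qualitative work. An analysis plan cannot restore this once the data are collected.

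Nothing in the design needs the arm to be known on Day 0, because the AI system is first used three months later.

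**Working it through.** The plan gives no figure on this point. Its sample size (61 per group) does not depend on it. The check is therefore a reading of the sequence, followed by simple arithmetic on the averaged end points.

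**Step 1: the sequence.**

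| Question | Source | Answer |
|---|---|---|
| What comes first? | Recruitment Process | Randomization, then visit 1 |
| Is this contradicted? | Table 2; Study Design and Setting | Randomization is shown within or at visit 1; neither puts the questionnaires ahead of it |
| Is anyone blinded? | Blinding | No, neither participants nor staff |
| Is the arm withheld for a time? | All sections | No such step is described |
| Is any patient-reported measure scheduled before randomization? | Table 2; qualitative Overview | No |
| Would measuring before randomization be barred? | Recruitment Process | No; only measuring before consent is barred |
| When is the arm first needed? | AI-Supported Care; Table 2 | Visit 2, month 3 |

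The plan as written thus collects the visit-1 measures after allocation. That the arm is known by then is an inference from the stated order, the lack of blinding and the absence of a withholding step.

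**Step 2: the weight of visit 1 in the end points.** CollaboRATE and CPS are scheduled at Day 0 and months 3, 6, 12 and 24. From inclusion to month 12 there are k = 4 visits, and to month 24 there are k = 5. Let b be the between-arm difference at visit 1 caused by knowing the arm. If each patient's end point is the mean of all k scheduled scores, then

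contribution to the between-arm difference = b / k.

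**Step 3: numbers.** The documents give no value for b. A range of 0.1 to 0.3 SD of a single-visit score is assumed here.

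| b (assumed) | Month 12, b/4 | Month 24, b/5 |
|---|---|---|
| 0.1 SD | 0.025 SD | 0.02 SD |
| 0.2 SD | 0.05 SD | 0.04 SD |
| 0.3 SD | 0.075 SD | 0.06 SD |

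The direction of b is unknown. Whatever its sign, it cannot reflect the AI output, because none exists at visit 1.

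**The case against.** **The moment of disclosure is not documented.** A reader might infer that every baseline answer is given by a patient, and every first consultation held by a physician, who knows the arm. The article does not say so. Recruitment is by study physicians who are not the treating physicians, and the AI first appears at visit 2, so the treating physician may not know the arm on Day 0. The full protocol may hold the detail. This stands, and it is why the wording here is *likely*. It does not remove the point, because the article itself states the order and describes no withholding step.

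**Physician behaviour.** One might suppose that physicians delay the conversation for AI-arm patients until a score is available. That is a hypothetical example, and nothing in the document supports it as fact.

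**Baseline adjustment.** One might also argue that adjusting for a contaminated visit 1 would bias the results. Statistical Analysis plans no baseline-adjusted model, so this harm arises only if such a model is added.

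**Size.** The shift is small, rests on an assumed b and concerns secondary end points. This is accepted. No effect on the primary end point is claimed.

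**A simpler remedy.** Leaving visit 1 out of the averages would remove the b/4 and b/5 terms without changing Day 0. That is true, but it would not restore the visit-1 questionnaires, interview and recording as measures taken before allocation.

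**Already acknowledged.** Strengths and Limitations concedes that "the open-label design, which is unavoidable, introduces the possibility of bias, especially since the primary end point is not a medical end point". This covers the period in which the AI is in use. It does not cover visit 1, where knowledge of the arm is avoidable.

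**Conclusion.** The point holds with limited size. The stated order, in an unblinded trial with no withholding step, makes it likely that the visit-1 patient-reported measures and the recorded consultation are collected with the arm known. Through the averaging in Textbox 1, a resulting difference b shifts the CollaboRATE and CPS comparisons by b/4 to month 12 and b/5 to month 24. With b between 0.1 and 0.3 SD, this is 0.025 to 0.075 SD and 0.02 to 0.06 SD. That is small, but it is systematic, would not shrink with more patients and can be avoided.

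The result rests on three assumptions: that the arm is disclosed at or soon after randomization, that b lies in the assumed range, and that all scheduled visits enter the mean with equal weight. Laboratory and demographic baseline values are little affected. The document does not support reading this as a threat to the validity of the trial or as a demonstrated bias in the primary end point.

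**What to change.** In Recruitment Process and Table 2, set the Day 0 order as:

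1. consent;
2. eligibility;
3. visit-1 consultation, questionnaires and interview;
4. randomization and disclosure of the arm.

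If randomization must stay earlier for practical reasons, state that the arm is not disclosed to patient or treating physician until the visit-1 measures are complete. If that is already the practice, one sentence saying so settles the point.

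For patients already enrolled under the present order, keep the data and run a sensitivity analysis without them. The Results section reports 19 of 122 enrolled on March 10, 2024 (19/122 = 15.6%). This is a snapshot; the number enrolled since then is not given, so the share who could still benefit is unknown.

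The cost is small. The patient must finish the visit-1 measures before randomization on the same day. The article does not describe clinic flow, so the local team should confirm that this is workable. No extra study visit is implied, and the start of AI support at month 3 is not delayed.
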